**3.2 Secondary Aims**

- Secondary objectives are to assess, in this population of vitamin D deficient individuals at high risk of type 2 diabetes, the effect of treatment on:
  1. Inflammatory markers;
  2. Adiponectin and osteocalcin;
  3. Insulin resistance using the revised Quicki index;
  4. Blood pressure;
  5. Lipid profile;
  6. Fasting free-fatty acid (FFA) levels;
  7. Body weight.
- We also seek to determine whether vitamin D requirements (to achieve a level of 25OHD ≥75 nmol/L) are influenced by fat mass (dual X-ray absorptiometry - DXA) in this population of overweight individuals.

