**5.5 Procedures**

Pre-randomisation measurements

To ensure the inclusion and exclusion criteria are met, a 24h urine collection for calcium and blood tests for 25OHD, calcium, albumin and renal function must have been done in the last month. A 75g 2h OGTT result no more than 3 months old must also be available.

Measurements at baseline and at the end of the study

*Anthropometrical and blood pressure assessments**

- Height (to the nearest 0.5 cm), using a wall-mounted stadiometer;
- Body weight (to the nearest 0.1 kg), measured without shoes and in light clothing, using an electronic calibrated scale;
- Waist circumference (to the nearest 0.5 cm), using a tape placed at the midpoint between the lower rib and the upper iliac crest;
- Blood pressure, taken 3 times in the sitting position with an adequate pressure cuff, after a 5-minute rest. The mean of the 3 results will be used for statistical purposes.

*These parameters will also be measured at 2 months

*Body composition*

Fat mass will be measured using dual-energy X-ray absorptiometry (Hologic, Discovery W, Bedford, MA, USA) only at the beginning of the study to correlate fat mass with the dose of vitamin D_3_ needed to reach optimal 25OHD levels.

*Biochemical assessments*

- Fasting blood will be drawn for 25OHD, total calcium, albumin, phosphate, PTH, alkaline phosphatase, osteocalcin, complete lipid profile, HbA_1_C, FFAs, adiponectin, high-sensitive C-reactive protein (hs-CRP) and fibrinogen;
- 2h OGTT after 75g of glucose: glucose, insulin and C-peptide levels will be measured at times -30, -20, -10, 0, 10, 20, 30, 60, 90 and 120 minutes;
- 24h urinary calcium and creatinine;
- Extra aliquot for storage for measurement of other bone markers and markers of inflammation (IL-6 and TNF-alpha) and diabetes when the funds will be available.

*Questionnaires*

- Medical history;
- Food questionnaire to estimate vitamin D and calcium intake [56];
- Physical activity questionnaire [57];
- Questionnaire to estimate sunlight exposure.

*Assessment of β-cell insulin secretion, insulin resistance and beta-cell function*

- **Insulin secretion rate** will be estimated by two methods:
  - The insulinogenic index ([Ins_t30_ – Ins_t0_] ÷ [Glucose_t30_ – Glucose_t0_]), which mainly reflects the first phase of insulin secretion;

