**5.6 Statistical analyses**

Analyses will be performed using SPSS version 15.0. Skewed data will be log-transformed or examined using non-parametric tests. Differences in delta HOMA-IR between the treatment and the placebo group will be compared by two-sample unpaired *t* test. The change in DI and in ISR (assessed by deconvolution analysis of C-peptide levels and the insulinogenic index) and also the total area under the curve of C-peptide by deconvolution analysis will be compared between groups with unpaired *t* test. Analyses will be performed to assess changes in inflammatory markers, intact osteocalcin, adiponectin, blood pressure, lipid profile, FFA and weight with a two-sample unpaired *t* test. A *P*-value of ≤0.05 will be considered statistically significant. The endpoints will be adjusted for risk factors of type 2 diabetes: age, sex, BMI, family history of type 2 diabetes and physical activity. The following covariates will also be adjusted for: sunlight exposure and VD and calcium intake. Finally, the variables that predict response to treatment will be identified with multiple linear regression analyses. We will perform data analysis on an intention-to-treat principle. We will also perform analysis on patients who achieved >75% compliance with study medication as well as those on active treatment who achieved target 25OHD levels ≥75 nmol/L.

*Sample size calculation*

Sample size calculation is based on the difference in delta HOMA-IR [0.15 ± 0.18 (SD)] observed in a similar population of overweight subjects with pre-diabetes before and after a mean weight loss of 9.8 kg [64]. This change in HOMA-IR resulted in improved beta-cell function and reduction in the area under glucose curve during OGTT. This change in HOMA-IR was therefore considered clinically significant and was chosen for sample size calculation. A sample of 32 participants in each group will have 90% power to detect a difference in delta HOMA-IR of 0.15 with a standard deviation of 0.18 and 2-sided alpha of 0.05. Assuming a drop out rate of 20%, we will study a total of 80 participants.

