**5.8 Potential sources of bias**

The main factors that could affect insulin sensitivity, and consequently, insulin secretion are physical activity and weight change. Physical activity will be evaluated with questionnaires at the beginning and at the end of the study. This factor will be taken into account in the analyses. However, some data suggest that calcium supplementation could induce weight loss [65, 66]. If significant weight loss is observed between the treatment and placebo group, it will be difficult to discriminate the beneficial effects of calcium and vitamin D on insulin sensitivity and secretion from those induced by weight loss. However, this will be adjusted for in multivariate analysis.

Seasonal variation can influence endogenous 25OHD production. With small number block randomisation, this effect will be minimised by distributing patients equally between treatment groups within a small time frame.

1. Dunstan, D.W., et al., *The rising prevalence of diabetes and impaired glucose tolerance: the Australian Diabetes, Obesity and Lifestyle Study.* Diabetes Care, 2002. **25**(5): p. 829-34.
2. Cameron, A.J., et al., *Overweight and obesity in Australia: the 1999-2000 Australian Diabetes, Obesity and Lifestyle Study (AusDiab).* Med J Aust, 2003. **178**(9): p. 427-32.
3. Giulietti, A., et al., *Monocytes from type 2 diabetic patients have a pro-inflammatory profile. 1,25-Dihydroxyvitamin D(3) works as anti-inflammatory.* Diabetes Res Clin Pract, 2007. **77**(1): p. 47-57.
4. Targher, G., et al., *Serum 25-hydroxyvitamin D3 concentrations and carotid artery intima-media thickness among type 2 diabetic patients.* Clin Endocrinol (Oxf), 2006. **65**(5): p. 593-7.
5. Cigolini, M., et al., *Serum 25-hydroxyvitamin D3 concentrations and prevalence of cardiovascular disease among type 2 diabetic patients.* Diabetes Care, 2006. **29**(3): p. 722-4.
6. Li, Y.C., et al., *1,25-Dihydroxyvitamin D(3) is a negative endocrine regulator of the renin-angiotensin system.* J Clin Invest, 2002. **110**(2): p. 229-38.
7. Billaudel, B., L. Barakat, and A. Faure-Dussert, *Vitamin D3 deficiency and alterations of glucose metabolism in rat endocrine pancreas.* Diabetes Metab, 1998. **24**(4): p. 344-50.
8. Tanaka, Y., et al., *Effect of vitamin D3 on the pancreatic secretion of insulin and somatostatin.* Acta Endocrinol (Copenh), 1984. **105**(4): p. 528-33.

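### Weight and blood pressure are measured at 2 and 6 months, but section 5.6 fixes a t test on one change score and gives the 2-month values no role in the intention-to-treat comparison

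*Protocol*

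**What the plan says.** - **Visits.** Section 5.5 lists anthropometry and blood pressure under "Measurements at baseline and at the end of the study". A footnote to that block adds: "These parameters will also be measured at 2 months". Weight and blood pressure therefore have two post-baseline values. The OGTT and the fasting lipids and FFA in the same section are listed only for baseline and the end.
- **Status.** Section 3.2 names blood pressure and body weight among the secondary objectives.
- **Test.** Section 5.6 assesses changes in a group of outcomes, among them "blood pressure, lipid profile, FFA and weight with a two-sample unpaired" t test. It does not say which visit the change runs to. The 6-month design and the baseline/end schedule make month 6 the natural reading.
- **Adjustment and analysis set.** Section 5.6 also says "The endpoints will be adjusted for risk factors of type 2 diabetes: age, sex, BMI, family history of type 2 diabetes and physical activity", and "We will perform data analysis on an intention-to-treat principle". It assumes 20% dropout without saying when it occurs, and names no method for missing values.
- **Use of weight elsewhere.** Section 5.8 discusses what follows "If significant weight loss is observed between the treatment and placebo group", and proposes multivariable adjustment.

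**The concern.** The protocol is not silent on method here. It names a test, and that test does not fit the visit schedule for these two outcomes. A two-sample t test on the 6-month change needs a 6-month value. A participant who attends at 2 months and then leaves has post-baseline data on weight and blood pressure, yet contributes nothing to the comparison unless something is imputed. Adjusting for age, sex, BMI and the other covariates does not bring that participant back, because the missing item is the outcome.

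Two things are at stake. One is precision: the 2-month value of a late leaver carries information about the 6-month value that the named test does not use. The other is bias: if leaving depends on how weight or blood pressure had moved by month 2, and does so differently in the two arms, a comparison of completers is distorted, while a model that includes the 2-month value corrects for that dependence.

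**Working it through.** **1. The plan's own figure.** Inputs from section 5.6: difference in delta HOMA-IR 0.15, SD 0.18, power 90%, "2-sided alpha of 0.05", 20% dropout.

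n per arm = 2 × (1.960 + 1.282)² × (0.18/0.15)² = 2 × 10.51 × 1.44 = 30.3, so 31 by the normal approximation. With the exact noncentral t, power is 0.898 at 31 per arm and 0.907 at 32, so the stated 32 reproduces. Then 32/0.8 = 40 per arm, 80 in total. All of this concerns HOMA-IR, which is not scheduled at 2 months, so nothing below changes it.

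**2. Who could be affected.** 20% of 40 is 8 per arm, 16 in total. Because the timing of dropout is not given, the number per arm with a 2-month but no 6-month value lies anywhere from 0 to 8.

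**3. Formula.** Let n₆ be the number per arm with a 6-month value and n₂ the number seen at 2 months. Let ρ be the correlation between the 2- and 6-month changes, and σ² the variance of the 6-month change. Under missing at random, the large-sample variance of the estimated 6-month mean in an arm is

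σ²(1 − ρ²)/n₆ + ρ²σ²/n₂ = (σ²/n₆) × (1 − ρ²f), with f = (n₂ − n₆)/n₂.

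The completers' t test has σ²/n₆. The variance ratio is therefore 1 − ρ²f, and the effective number per arm is 32/(1 − ρ²f).

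**4. Results.** n₆ = 32. The values of ρ and the share of leavers going after month 2 are assumptions; the protocol gives neither.

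| Leavers going after month 2 | f | ρ | Variance ratio | Effective n per arm | CI narrower by |
|---|---|---|---|---|---|
| none | 0 | any | 1.000 | 32.0 | 0% |
| half (4 of 8) | 4/36 = 0.111 | 0.5 | 0.972 | 32.9 | 1.4% |
| half | 0.111 | 0.7 | 0.946 | 33.8 | 2.8% |
| half | 0.111 | 0.8 | 0.929 | 34.4 | 3.6% |
| all (8 of 8) | 8/40 = 0.20 | 0.5 | 0.950 | 33.7 | 2.5% |
| all | 0.20 | 0.7 | 0.902 | 35.5 | 5.0% |
| all | 0.20 | 0.8 | 0.872 | 36.7 | 6.6% |

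If all leave late, this equals 64/0.950 = 67 to 64/0.872 = 73 completers in place of 64, or about 3 to 9 more. Stretching ρ to 0.9 with all leaving late gives 1 − 0.81 × 0.20 = 0.838, an effective 38.2 per arm and an interval 8.5% narrower. For participants with both visits the 2-month value adds little to the 6-month contrast; the gain comes from late leavers.

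**5. Bias.** The direction of the argument is clear: conditioning on the observed 2-month value removes bias from dropout that depends on that value. Its size would need the SD of weight change, the dropout mechanism and its difference between arms. The protocol gives none of these, so no figure is offered.

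**The case against.** **Missing-data handling belongs in the SAP.** That document is not at hand, and rules for missing 6-month values and interim visits are commonly placed there. An unpaired t test on change is also a valid analysis in a randomised trial. This has weight, and it is why the point is a cheap improvement and not an error in the trial. It does not dispose of the point: section 5.6 chooses a method, and an SAP would have to supplement or override it.

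**The 2-month values are not necessarily lost.** A reader might infer that they cannot be used, will be discarded, or that every late leaver is dropped. The documents do not say so. A t test could be run on the 2-month change, or on a 6-month change imputed with the help of month 2. The text simply assigns these values no role, and exclusion follows only if the test is applied to the 6-month change without imputation.

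**Section 5.8 might seem to raise the stakes.** A reader might infer that the reading of the insulin results hangs on this weight test, since the section asks whether weight loss differs between arms. Its remedy, however, is adjustment in the multivariable analysis. Late leavers have no 6-month insulin outcome, so adding them to a weight model leaves that adjustment unchanged. This objection stands.

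**A definite bias in kilograms might be inferred.** Selective dropout in one arm, driven by 2-month weight change, would shrink or inflate the completers' difference. A simulation built on that mechanism will show recovery by construction. Nothing in the protocol indicates such dropout in a double-blind placebo trial.

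**Conclusion.** The point holds in limited form. For two secondary endpoints measured at three visits, section 5.6 fixes a single-change t test, leaves the time point unnamed and gives the 2-month values no role. Applied to the 6-month change without imputation, it omits randomised participants who have usable post-baseline data, which fits poorly with intention to treat.

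The precision at issue is modest: a variance reduction of about 5-13% if all dropout falls after month 2, about 3-7% if half does, and zero if none does. This rests on the plan's 20% dropout, equal in both arms, an assumed correlation of 0.5 to 0.8, and data missing at random. Protection against dropout related to the 2-month value is a further benefit, of a size the documents do not allow one to state. The primary insulin outcomes, the 80 participants and the 90% power are untouched. The change is still worth making because it uses data already scheduled and costs almost nothing.

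**What to change.** In section 5.6, take weight and blood pressure out of the list of outcomes tested by unpaired t test and add a sentence to this effect: weight, systolic and diastolic blood pressure will each be analysed with a mixed model for repeated measures, with the 2- and 6-month values as outcomes and baseline value, arm, visit and arm-by-visit as terms; all randomised participants with at least one post-baseline value will be included, and the arm difference at 6 months will be reported.

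This names the time point and aligns the analysis more closely with the stated principle. The cost is one sentence and slightly more analysis work, with no new data. The model relies on missing at random given the baseline and 2-month values, which is in general no stronger than what a completers' t test needs to be unbiased. Participants with no post-baseline value would still be absent.

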**5.2 Randomisation and Intervention**

The proposed study is a prospective, double blind, randomised and placebo controlled 6-month clinical trial. Subjects will be randomly assigned to one of two groups, with stratification according to sex, age (< or >50 years of age) and BMI (< or >30). The treatment group will receive vitamin D_3_ (cholecalciferol) 2000 IU plus calcium carbonate (1200 mg elemental Ca daily) and the control group will take placebo pills. Permuted blocks of 4 treatment allocations will be used to ensure that after each 4^th^ allocation there are equal numbers in each treatment arm. After 8 weeks of treatment, if subjects in the treatment group have 25OHD levels less than 75 nmol/L, the dose of cholecalciferol will be increased to 4000 IU daily to reach optimal levels. On the other hand, subjects in the placebo group and those in the treatment group that reached optimal levels of 25OHD will be given extra placebo pills. To ensure blinding is respected, a person external to the study will look at the 8-week 25OHD results and contact patients to add an extra cholecalciferol or placebo pill to their regime, as appropriate.

The dosage of cholecalciferol has been estimated from the study of Barger-Lux and al., a rigorous trial performed in healthy overweight men [52]. They showed that each mcg (40 IU) of vitamin D_3_ increase the 25OHD concentration by 0.70 nmol/L. Based on the mean 25OHD level reported in populations of obese vitamin D deficient subjects (30 nmol/L) [25, 50, 53] and the expected increment described previously, it can be estimated that 2400 IU daily of vitamin D_3_ would be needed to increase the mean 25OHD level of our population to over 75 nmol/L. Of note, the dose-response relationship was not affected by body weight or fat mass. However, other data suggest that vitamin D requirements might be higher in obese compared to normal weight subjects [54]. Therefore, given that participants in our study will be obese, if adequate 25OHD levels are not reached after 8 weeks, the dose of cholecalciferol will be increased to 4000 IU daily. This dose, given daily for 3 months to 28 healthy adults, increased mean 25OHD levels from 37.9 ± 13.4 nmol/L to 96.4 ± 14.6 nmol/L [55]. None of the subjects had 25OHD levels <75 nmol/L at the end of the study.

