  - The deconvolution analysis of C-peptide levels after a glucose load. C-peptide is probably a better indicator of insulin secretion than insulin itself since the latter is subject to hepatic clearance. Pre-hepatic ISR will be calculated from deconvolution of peripheral plasma C-peptide levels using a two compartment mathematical model with standard parameters for C-peptide distribution and metabolism, as previously described using the Chronobiological Series Analyses software (iBridge Network, [www.iBridgeNetwork.org](http://www.iBridgeNetwork.org), University of Chicago) [58]. Use of standard parameters for C-peptide clearance and distribution has been shown to result in insulin secretion rates that differ in each subject by only 10-12% from those obtained with individual parameters and there is no systematic over- or underestimation of insulin secretion. Incremental ISR from baseline during the first 30 minutes divided by incremental glucose and absolute total area under the curve of C-peptide by deconvolution analysis will be compared between baseline and 6 months of treatment.
- **Insulin resistance** will also be assessed by two methods:
  - The homeostasis model assessment for insulin resistance (HOMA-IR) is particularly suitable for obese and/or glucose intolerant subjects and has been shown to highly correlate with measures of insulin sensitivity obtained from the gold-standard procedure (euglycemic clamp technique) [59-61]. It is calculated from fasting insulin and glucose levels as follows: [Fasting insulin (mU/L) X fasting glucose (mmol/L)] ÷ 22.5.
  - Insulin resistance will also be estimated with the revised Quicki index: 1/[log (fasting glucose in mg/dl) + log (fasting insulin in μunits/ml) + log (fasting FFA). This index was shown to better correlate with euglycemic clamp than HOMA-IR in impaired glucose tolerant individuals (r=0,802) [62].
- **Beta-cell function** will be estimated by calculating the disposition index (DI): DI = insulin sensitivity (HOMA-IR) X ISR (deconvolution analysis of C-peptides).

*Evaluation of compliance*

Pill count will be performed after two months and at the end of the study to verify compliance to medication. Participants will be asked to report any change in their medication since the last visit.

*Monitoring of side effects and Safety Issues*

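### The sample size rests on a HOMA-IR change of 0.15 ± 0.18 whose scale is not stated; read as untransformed HOMA-IR, the SD looks implausibly small and the 90% power is very fragile

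*Protocol*

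**What the plan says.** Section 5.6 (sample size calculation) takes its inputs from one cited weight-loss study: "the difference in delta HOMA-IR [0.15 ± 0.18 (SD)] observed in a similar population of overweight subjects with pre-diabetes", measured "before and after a mean weight loss of 9.8 kg". It regards this change as clinically significant because beta-cell function and the OGTT glucose area also improved. From these inputs it concludes that 32 participants per arm have "90% power to detect a difference in delta HOMA-IR of 0.15 with a standard deviation of 0.18", with "2-sided alpha of 0.05". Allowing 20% dropout, it plans 80 participants.

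Section 5.5 defines the endpoint without transformation: "Fasting insulin (mU/L) X fasting glucose (mmol/L)] ÷ 22.5". Section 5.6 compares the change in HOMA-IR between arms by an unpaired t test. A general sentence at the start of 5.6 allows log transformation or non-parametric tests for skewed data.

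The protocol gives no baseline HOMA-IR, no fasting insulin level and no other estimate of variability.

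**The concern.** HOMA-IR comes first in the primary aim (section 3.1) and is the only basis for the sample size. Converted to insulin by the protocol's own formula, both the target and its SD are fractions of 1 mU/L. That SD has to cover assay error, day-to-day variation in insulin and glucose, and individual drift over six months, in people with a BMI of 25 to 40 and glucose intolerance. The target also looks small for the effect of losing 9.8 kg.

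Either the figures are raw and the SD is surprisingly small, or they belong to a transformed scale that the endpoint and test do not name. In both cases the stated 90% power cannot be tied to the analysis as written. A null result would then be read against a power that may not apply.

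**Working it through.** **Inputs from the protocol.** Difference 0.15, SD 0.18, two-sided alpha 0.05, 90% power, 32 per arm, 20% dropout (5.6). 1:1 allocation (5.2). HOMA-IR = insulin × glucose ÷ 22.5 (5.5). Fasting glucose below 7.0 mmol/L (5.3).

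**Assumptions.** Fasting glucose 5.0 to 6.9 mmol/L. Baseline HOMA-IR 2 to 5.3; at glucose 6 mmol/L this is fasting insulin of 7.5 to 20 mU/L (20 × 6 ÷ 22.5 = 5.3). Any SD other than 0.18 is also an assumption.

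**1. The plan's own figure.** Normal approximation: n = 2 × (1.96 + 1.2816)² × 0.18² ÷ 0.15² = 30.3, so 31 per arm. With the noncentral t, 31 per arm gives 89.8% and 32 gives 90.7%. Total: 64 ÷ 0.8 = 80. The stated figures reproduce.

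**2. Conversion to insulin, glucose held fixed** (HOMA units × 22.5 ÷ glucose).

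| Fasting glucose (mmol/L) | 0.15 in mU/L | 0.18 in mU/L |
|---|---|---|
| 5.0 | 0.68 | 0.81 |
| 5.5 | 0.61 | 0.74 |
| 6.0 | 0.56 | 0.68 |
| 6.9 | 0.49 | 0.59 |

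**3. Within-person variation that an SD of 0.18 allows.** If the two visits vary equally and independently, and individuals do not differ in response, the per-visit SD is 0.18 ÷ √2 = 0.127. As a CV this is 0.127 ÷ 2 = 6.4% at HOMA-IR 2, 4.2% at 3, 3.2% at 4 and 2.4% at 5.3, assay error included. Glucose alone can use it up: with insulin fixed at 15 mU/L, an SD of 0.27 mmol/L for the change in glucose already gives 15 × 0.27 ÷ 22.5 = 0.18.

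**4. Power if 0.15 is a raw target** (noncentral t, 32 per arm).

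| SD of change | Power for 0.15 | n per arm for 90% | Difference detectable with 90% |
|---|---|---|---|
| 0.18 | 90.7% | 32 | 0.15 |
| 0.25 | 66% | 60 | 0.21 |
| 0.30 | 50% | 86 | 0.25 |
| 0.50 | 22% | 235 | 0.41 |

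Power falls below 90% above an SD of 0.182 and below 80% above 0.211. With no dropout (40 per arm) these limits are 0.204 and 0.237.

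**5. Power if the figures are on log10.** The target is a fall of 1 − 10^(−0.15) = 29%. A t test on change in log10 HOMA-IR keeps 90.7%, because 0.15 ÷ 0.18 is unchanged. For a t test on raw change, take the effect as 0.292 × baseline and the SD as √2 × CV × baseline. Baseline cancels, so the standardised effect is 0.292 ÷ (√2 × CV). Power at 32 per arm is 98% at a CV of 20%, 90% at 25% and 77% at 30%. An SD of 0.18 on log10 itself implies a CV of about 30%: 0.127 × 2.303 = 0.293 on the natural log, and √(e^(0.293²) − 1) = 0.30. So even on this reading the choice of test scale matters somewhat.

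**The case against.** The strongest reply is that nothing in the protocol contradicts 0.18. It is the only SD given, the calculation from it is right, and every alternative SD, CV or baseline HOMA-IR above is assumed. The source study cannot be consulted here. This stands. A reader might infer that the trial almost certainly lacks its stated power, and the document does not support that. A severe shortfall arises only if 0.15 is truly raw and 0.18 is too small, yet both numbers are reported from the same result.

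Second, if the figures are on log10, the raw target is not 0.15 but about 29% of baseline, for example 0.88 at HOMA-IR 3. Power is then largely intact, as step 5 shows. Pairing a larger raw SD with 0.15 would mix scales under that reading. This also stands.

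Third, 5.6 allows skewed data to be log-transformed, so it is too firm to say that the protocol commits to a raw-scale t test. That is fair, but it does not close the gap. If HOMA-IR is logged, a raw target and raw SD no longer describe the test; if the figures are already logged, neither the endpoint in 5.5 nor the target in 5.6 says so.

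That a statistical analysis plan may exist does not settle the matter. The scale of the sample-size inputs belongs to the calculation that fixed 80 participants, and that calculation is in the protocol.

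**Conclusion.** The point holds in a limited form. There is no arithmetic error, and the document does not show that the trial is underpowered. It does show that the scale of 0.15 ± 0.18 is unstated. It also shows that, read with the protocol's own definition of HOMA-IR, the SD is 0.59 to 0.81 mU/L of insulin, or a within-person CV of 2.4 to 6.4% per visit at an assumed HOMA-IR of 5.3 to 2. That looks implausibly small for a 6-month change in this population.

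On the raw reading the power has almost no reserve: a rise in SD from 0.18 to 0.25 takes it from 91% to 66%. On the log10 reading the power survives, but endpoint, target and test need to be put on that scale. That log10 is the more natural fit to a 9.8 kg weight loss is an inference, not something the protocol states. The matter should be corrected; confidence is medium because the source is not available.

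**What to change.** Check the cited source and state in 5.6 the scale of 0.15 and 0.18.

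- **If log:** state the base, define the primary endpoint and its t test as change in log HOMA-IR, and give the target as a ratio (on log10, 0.71, a 29% fall).
- **If raw:** justify the SD, and restate the power or the detectable difference for 64 completers over a range of SDs of change. A baseline SD alone does not give the SD of change: under equal variances the two are linked by √(2(1 − ρ)), where ρ is the baseline to 6-month correlation. The factor is 1.0 at ρ = 0.5 and 0.45 at ρ = 0.9, and the protocol gives no ρ.

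In either case, compute HOMA-IR from the mean of the −30, −20, −10 and 0 minute values. Section 5.5 already provides them: "glucose, insulin and C-peptide levels will be measured at times -30, -20, -10, 0, 10, 20, 30, 60, 90 and 120 minutes". Averaging four samples reduces within-visit noise, and halves its SD (√4 = 2) only if the samples vary independently. It does nothing for between-day variation, so it complements a stated scale and does not replace it.

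The cost is a reworded sample-size paragraph and endpoint definition and, on the raw reading, possibly a less favourable stated power. No extra participants, visits or blood samples are needed.
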